### Analysis Plan

The cluster randomized trial design will be used by randomizing primary care physicians (PCP) into the intervention or usual care arms. Outcomes will be collected and analyzed at the patient level. We will examine assigned randomization against the computer-generated randomization scheme to ensure randomization validity. Patient characteristics between the two groups will be compared using mixed effects models for continuous variables and generalized estimating equations for categorical variables while adjusting for random PCP effects. We will examine the distributions of continuous variables and use alternative approaches such as transformation or nonparametric methods in cases of violation to the normal distribution assumption. We will also examine the frequency distribution of all categorical variables and adopt exact inference procedures in cases of zero or small cell size. Any baseline variable that is found to be significantly different between the two groups will be included as a covariate in the analyses outlined below.

An intension to treat approach will be used in the analysis of all outcome measures. Composite cognitive scores collected at 6, 12, 18 and 24 months will be used as the primary outcome variables in mixed effects models. An indicator variable for intervention group (intervention vs usual care), time, interaction between group and time, and baseline cognitive scores will be included as independent variables as well as significant factors from the baseline comparison. PCP will be used as random effects to adjust for within-physician correlations. Significant group and time interaction or significant group main effect will indicate differences in cognitive function between the two groups. If significant interactions between group and time are found, post-hoc analyses will be conducted to determine the times when the two groups have significantly different cognitive scores. A significant main group effect in the absence of a group-by-time interaction would indicate differences between groups in cognitive function at all follow-up time points.

In a second set of models, we will determine whether differences between groups were accounted for by decreases in total exposure to anticholinergics from baseline to 24 months. For each medication, standardized daily exposure will be calculated using standardized daily dose as in the study by Gray^7^ and validated in our prior work^14
17

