### Sample Size and Rationale

The sample size calculation was conducted using a mixed effects model and adjusting for the cluster randomization design. Assuming a within-subject correlation of 0.3, 0.2 and 0.1 for outcomes observed 6, 12 and 18 months apart, respectively, from the same individuals over time, 96 patients per group is required for 80% power to detect differences in composite cognitive scores of 0.6 SD at 24 months between the intervention and usual care groups with type I error rate at α=0.05 assuming linear trends in cognitive change in both groups. We further assume an intra-class coefficient (ICC) of 0.05 for primary care physicians and an average of 6 patients per physician. Accounting for the cluster design requires 120 patients per group to complete the trial. With an expected 30% attrition rate, we plan to enroll 172 patients per group into the study. Prior studies have reported mean differences in 1-year change of cognitive scores of 1.82 (SD 17) or 1.93 (SD 15) between those on definite anticholinergics versus those non-users. The effect sizes we used assume that our intervention will be able to detect a one-sixth reduction in expected cognitive decline if patients in the intervention group discontinue anticholinergics. Our assumption on the ICC is based on prior studies on prescribing patterns in physicians and practices.^58^

In Primary Aim 2, using the effective sample size of 96 patients per group accounting for the design effect from cluster randomization, we will have 85.6% power to estimate the confidence bands with half-width of 0.3 SD for the differences in symptom scores from PROMIS and HUI scores between the intervention and usual care groups during follow-up using the two-sample t-tests at the 0.05 level. Power estimates were calculated using the GLMPower and Power procedures in SAS software version 9.4 (SAS Institute, Cary, North Carolina).

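### A significant main effect with a non-significant group-by-time interaction is to be read as a difference at every visit; this does not follow and can produce unsupported, or with a delayed effect false, claims at early visits

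*Protocol article*

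**What the plan says.** The Analysis Plan of the protocol article sets the outcome and model: "Composite cognitive scores collected at 6, 12, 18 and 24 months will be used as the primary outcome variables in mixed effects models". Group, time, their interaction and the baseline score are independent variables, with a random physician effect. Either of two results counts as evidence: "Significant group and time interaction or significant group main effect will indicate differences in cognitive function between the two groups".

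Two reading rules follow. After a significant interaction, visits are examined: "If significant interactions between group and time are found, post-hoc analyses will be conducted to determine the times" at which the groups differ. Otherwise, a significant "main group effect in the absence of a group-by-time interaction would indicate differences between groups in cognitive function at all follow-up time points".

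Significance is the only criterion given for the interaction, so its absence can only mean a non-significant test. The same section says that PROMIS and HUI scores will be modelled in a similar way, so the rule appears to carry over to them.

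Sample Size and Rationale plans on 0.6 SD at 24 months, "assuming linear trends in cognitive change in both groups".

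**The concern.** The rule takes two steps that do not follow. First, it treats failure to reject the interaction as evidence that the effect is constant. Second, it moves from a significant main effect to a difference at each visit. If the main effect is the average over visits (its coding is not stated), it can be carried entirely by the later visits.

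The rule also sits badly with the sample size section, where the planned alternative is a gap that widens with time. A constant difference is not what the design expects.

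At stake is the statement of when benefit appears. Study Design presents the long follow-up, and the ability to see trends up to 24 months, as a distinctive feature of the trial. Under the rule, a 6-month difference could be declared on the strength of the 18- and 24-month data, in exactly the case where the article promises no visit-level comparison to check it.

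**Working it through.** **Inputs** (Sample Size and Rationale). "Assuming a within-subject correlation of 0.3, 0.2 and 0.1 for outcomes observed 6, 12 and 18 months apart"; "96 patients per group is required for 80% power to detect differences in composite cognitive scores of 0.6 SD at 24 months"; α = 0.05; ICC 0.05; 6 patients per physician.

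**The plan's own figures.** 96 × (1 + 5 × 0.05) = 120, and 120 / 0.70 = 171.4, rounded up to 172. Both match the article. The base of 96 cannot be reproduced uniquely, because neither the tested contrast nor the start of the linear trend is given. It is used here only as the effective sample size.

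**Assumptions.** Two-sided tests, known covariance, no missing data, main effect equal to the average of the four visit differences. The interaction is tested in two ways, since the coding of time is not stated: with 3 df (time categorical) and as a linear slope.

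**Two variance models.** R is the 4 × 4 correlation matrix and J a matrix of ones.

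- Model A: V = (2/96) R. The cluster penalty is spread over all contrasts.
- Model B: V = (2/120)(R + 5 × 0.05 J). The physician intercept is constant over time.

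**Average over visits.** The variance factor is [4 + 2(3 × 0.3 + 2 × 0.2 + 0.1)] / 16 = 6.8/16 = 0.425.

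- A: SE = √(2/96 × 0.425) = 0.094
- B: SE = √(2/120 × (0.425 + 0.25)) = 0.106

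**Slope**, weights (−3, −1, 1, 3). The variance factor is 18.8, and the constant intercept in B cancels.

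- A: SE = √(2/96 × 18.8) = 0.626
- B: SE = √(2/120 × 18.8) = 0.560

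The average and the slope are uncorrelated under R, so with the slope test P(rule fires) = P(main significant) × [1 − P(slope significant)].

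**Linear divergence from baseline, 0.15/0.30/0.45/0.60.** The mean difference is 0.375 and the slope contrast is −0.45 − 0.30 + 0.45 + 1.80 = 1.5.

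- A: main z = 0.375/0.094 = 3.99, power 0.979; slope z = 1.5/0.626 = 2.40, power 0.669. The rule fires in 0.979 × 0.331 = 0.324.
- B: main z = 3.54, power 0.942; slope z = 2.68, power 0.764. The rule fires in 0.942 × 0.236 = 0.222.
- With 3 df, interaction power is 0.50 (A) and 0.60 (B), and the rule fires in 0.49 and 0.38 (400,000 simulated sets of visit differences).

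The interaction test therefore misses this divergence in 33 to 50% of trials (A) or 24 to 40% (B). The 6-month contrast alone has 18% power for 0.15 SD. Among trials where the rule fires, it is significant in 30 to 40% (A) or 34 to 45% (B).

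**How often the rule fires, by true shape** (ranges run over the two interaction tests):

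| True differences (6/12/18/24 months) | Model A | Model B | 6-month statement |
|---|---|---|---|
| 0.15/0.30/0.45/0.60 | 32–49% | 22–38% | true, but unsupported |
| 0/0.2/0.4/0.6 | 10–20% | 4–11% | false |
| 0/0.3/0.3/0.3 | 42–47% | 31–36% | false |
| 0.3 at every visit | 85% | 77% | true |
| 0 at every visit | just under 5% | just under 5% | false |

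**The case against.** The strongest defence is that the sentence is conditional. If there truly is no interaction, an additive model does give the same difference at every visit, and the statement is then correct. That stands. The fault lies in deciding absence by a non-significant test, which is the only criterion the article gives.

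A reader might infer that the rule would generate false claims of early benefit under the plan's own assumptions. The document does not support that. Linear trends from groups equal at baseline give a real 6-month difference of 0.15 SD, so the claim is unsupported rather than false. The shapes with zero at 6 months are assumptions of this review. The Deprescribing Intervention section expects most deprescribing to be complete four to six weeks after enrolment, so an early effect is quite possible.

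Model A also overstates the problem if the physician effect is constant over time, because that effect cancels from the interaction. Model B is therefore shown alongside, and for 0/0.2/0.4/0.6 the lower end of its range is below 5%.

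Nor can it be said that the trial could not show when an effect appears: visit comparisons follow a significant interaction, which happens in 50 to 67% (A) or 60 to 76% (B) of trials under linear divergence. The article also does not say that visit-level estimates will be withheld, and an analysis plan not shown may tabulate them. The stated inference rule would still be wrong.

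**Conclusion.** The point holds as a fault in a stated rule of interpretation. A non-significant interaction is not evidence of a constant effect, and at the planned size the test would miss the linear divergence 0.15/0.30/0.45/0.60 SD in roughly a quarter to a half of trials. Under that divergence the rule yields visit-level claims that the early data usually do not support by themselves. It yields false early claims above the nominal 5% only if the effect is delayed, and then at a rate that depends heavily on the shape and on the variance model. With no effect at any visit the rate stays just under 5%, and with a constant effect the reading is true.

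The consequence is confined to statements about particular visits; this sentence does not alter the test of any group difference. The figures rest on the article's correlations, ICC and sample size and on the assumptions listed with the calculation. The change should be made, but the primary comparison does not depend on it.

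**What to change.** Delete the sentence. In its place, state that:

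- the model-estimated group difference with its 95% CI will be reported at 6, 12, 18 and 24 months, whatever the interaction p-value;
- a significant main effect will be described as an average over follow-up, with its coding defined so that this is what it estimates;
- any statement about a particular visit will rest on that visit's contrast.

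Apply the same wording to the PROMIS and HUI models. The article names no primary visit, so this repair does not depend on choosing one.

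The cost is a change of wording and four estimate statements in the model already planned. No new data and no change in sample size are needed. The article expects data collection to run to July 2026.

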33^ in which the daily dose is divided by the minimum effective dose. Days of standardized exposure for each medication will be the sum of the standardized days of exposure in a time period that includes each medication for each patient. This exposure is defined analogously to the pack-years concept used to characterize exposure to cigarette smoking and is a cumulative measure reflecting both exposure intensity and duration. Total exposure will be compared between the two groups using mixed effects models with group (intervention and control) as the independent variable adjusting for significant baseline variables and random PCP effects. We will then use the mixed effect model with cognitive scores at 6, 12, 18, and 24 months as outcome variables described above with total anticholinergic exposure as an additional independent variable adjusting for baseline cognitive scores and PCP random effects. Attenuation of the intervention effect from the original model would indicate that the effect of intervention is mediated through the reduction in anticholinergic exposure. Comparisons of PROMIS scores and HUI will be conducted similarly to the models we described above for cognitive scores. Exploration of potential moderation effects from *APOE*, or participants’ characteristics will be conducted by including each of these variables and its interaction with the randomization group in the mixed effects models for the outcome measures. Significant interactions will indicate significantly different intervention effects in subgroups defined by *APOE*, or participants’ characteristics.

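### The mediation rule reads any attenuation as mediation, and on its plain reading it adjusts cognition at 6, 12 and 18 months for drug use that came later

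*Protocol article*

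**What the plan says.** Everything quoted here is from the Analysis Plan section of the protocol article. A second set of models asks whether "differences between groups were accounted for by decreases in total exposure to anticholinergics from baseline to 24 months". The exposure "is a cumulative measure reflecting both exposure intensity and duration", and for each drug it is "the sum of the standardized days of exposure in a time period that includes each medication for each patient". It is first compared between arms: "Total exposure will be compared between the two groups using mixed effects models with group (intervention and control) as the independent variable". No time term is mentioned in that comparison.

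The plan then returns to the "mixed effect model with cognitive scores at 6, 12, 18, and 24 months as outcome variables", this time "with total anticholinergic exposure as an additional independent variable adjusting for baseline cognitive scores and PCP random effects". The inference follows directly: "Attenuation of the intervention effect from the original model would indicate that the effect of intervention is mediated through the reduction in anticholinergic exposure".

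The same section also carries into the later analyses any baseline variable that differs significantly between the arms. The full adjustment set is therefore baseline cognition, a physician random effect, and whichever baseline variables happen to be significantly imbalanced.

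**The concern.** Randomisation supports a conclusion about the intervention as a package: education, pharmacist contact, and substitution or withdrawal of drugs. To say that the effect runs through lower anticholinergic exposure, the trial needs this second analysis. The Discussion presents the causal link between these drugs and cognition as what the study will contribute, so the inference rule matters.

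As written, the rule has three weaknesses.

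- **Time order.** A total to month 24, used as a predictor of cognition at month 6, consists mostly of drug use that had not yet happened. If earlier cognition influences later prescribing, the covariate is partly a consequence of the outcome.
- **Confounding.** Exposure during follow-up is determined by health, symptoms and clinical decisions. The Deprescribing Intervention section itself expects the process to be interrupted or delayed according to clinical context. Selecting covariates by significant baseline imbalance picks up chance differences between arms, not common causes of exposure and cognition.
- **Decision rule.** A fall of any size in the group coefficient satisfies the sentence.

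The result could be mediation reported where there is none. If the dependence runs the other way, for example if declining patients are taken off these drugs, real mediation could be hidden.

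**Working it through.** The plan gives no figure for this analysis, so there is none to reproduce.

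**1. Exposure window against outcome visit.** Inputs: a window of 0 to 24 months and visits at 6, 12, 18 and 24 months (Analysis Plan). The share of the window after visit *t* is (24 − *t*)/24.

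| Visit (months) | Calculation | Share after the outcome |
|---|---|---|
| 6 | 18/24 | 75% |
| 12 | 12/24 | 50% |
| 18 | 6/24 | 25% |
| 24 | 0/24 | 0% |

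These are shares of calendar time. They do not measure bias, and month 24 is not affected.

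**2. How often chance alone gives attenuation.** Suppose exposure has no effect on cognition and there is no confounding. Adding it then changes the group coefficient by an amount that is symmetric about zero and independent of the unadjusted estimate.

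- If the group effect is large relative to the noise, the change is toward zero in about 1/2 of trials.
- If there is no group effect, the probability is arctan(2σ/τ)/π, where σ is the SD of the unadjusted estimate and τ the SD of the change. With τ = σ this is arctan(2)/π = 1.107/3.142 = 0.35. It approaches 1/2 as τ becomes small relative to σ.

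Hence up to about half.

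**3. Whether the rule separates mediation from other explanations.** A simulation used 2000 trials with 120 patients per arm, 6 patients per physician and four visits. Those counts are from Sample Size and Rationale and the visit schedule. The physician variance was set at 0.05; in the simplest scenario this is an ICC of 0.05/(0.16 + 0.05 + 0.49) = 0.07, close to the plan's 0.05. Group effects were estimated by least squares on the stacked visits. All effect strengths are assumptions, not figures from the document: a group effect of 0.30 not acting through exposure in A to C, and an exposure effect of −0.2 per unit with no direct effect in D.

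| Scenario | Group effect, unadjusted | After adding 24-month total | After adding exposure up to each visit | Trials with a smaller estimate (24-month total) |
|---|---|---|---|---|
| A. No exposure effect, no confounding | 0.30 | 0.30 | 0.30 | 51% |
| B. No exposure effect, unmeasured common cause | 0.30 | 0.01 | 0.08 | 100% |
| C. No exposure effect, poorer earlier cognition raises later exposure | 0.30 | −0.03 | 0.26 | 100% |
| D. True full mediation | 0.25 | 0.00 | 0.00 | 100% |

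If attenuation means closer to zero in absolute value, the shares are 51%, 94%, 94% and 91%. In C at month 6 alone, 0.30 becomes −0.11.

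Three things follow. The rule cannot tell B or C from D. Aligning exposure with the visit removes most of the distortion in C (0.26 against 0.30) but not in B (0.08), so timing alone is not a sufficient repair. The sizes, and the direction of the shift, depend on the assumed strengths and signs: if the dependence in B or C is reversed, the adjusted effect moves away from zero.

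**The case against.** The strongest reply has five parts.

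- **The exposure window is inferred.** The text refers loosely to a time period, and medication is self-reported at every assessment with orders extracted across the 24 months, so visit-specific exposure is possible. This stands in part: a single total is not stated outright. It is still the plain reading, given the phrase "accounted for by decreases in total exposure to anticholinergics from baseline to 24 months" and a between-arm comparison with no time term. If something else is meant, the text should say so.
- **Most deprescribing is expected within four to six weeks.** Early and total exposure may then be closely related. This stands as a reason not to treat the calendar shares as bias. It does nothing about confounding or the decision rule.
- **Intervals, confounder lists and bootstraps belong in an SAP.** Their absence alone would be no criticism. But the article goes further and states an inference rule, and that rule is faulty as stated.
- **The adjustment set is wider than baseline cognition and physician.** A reader might infer that nothing else is adjusted for. That is wrong, because significantly imbalanced baseline variables are added. Prior exposure or comorbidity would enter only by that route.
- **Mediation is not among the objectives listed at the start of Methods.** This is correct, and the primary comparison does not depend on it. That limits the importance of the point without removing it.

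A reader might also infer that low exposure partly reflects early exit. Death would shorten a raw sum, but the document does not say that record extraction stops at withdrawal or that exposure is left unscaled for follow-up, so this is not established.

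**Conclusion.** The concern holds for the mediation inference only. The stated rule accepts any attenuation, relies on an exposure that is not randomised, and on its plain reading uses drug use after the outcome at three of the four visits. It cannot distinguish mediation from chance, confounding or reverse causation.

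Two stronger readings should be avoided. The plan says attenuation would indicate mediation; it does not call it proof. And about 50% is not a general false-positive rate: it is roughly the upper limit for chance alone, when exposure has no effect, nothing confounds it, and the group effect is large relative to the noise (or the change in the coefficient is small relative to it). With no group effect it is about 35% when the change is as variable as the estimate itself. Under confounding or feedback in the direction simulated, the rule was met in 94% to 100% of trials, but those figures rest on assumed strengths.

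The randomised intention-to-treat comparison is unaffected. This should be corrected before analysis, but it does not threaten the primary result.

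**What to change.** Four changes to the Analysis Plan:

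1. Define exposure for each outcome as the amount accumulated from randomisation up to that visit (0–6, 0–12, 0–18 and 0–24 months).
2. Adjust for prespecified baseline confounders whether or not they are imbalanced: prior-year anticholinergic exposure, age, education, number of medications and comorbidities.
3. Report the indirect effect with a 95% CI that respects physician clustering, for example from a bootstrap that resamples physicians.
4. Replace the attenuation sentence with wording such as: *Mediation through reduced exposure will be claimed only if the 95% CI for the indirect effect excludes zero, and will be described as conditional on no unmeasured confounding of exposure and cognition.*

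The condition in the fourth change is needed because an interval guards against chance, not against an unmeasured common cause (scenario B).

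No new data are required. Medication is self-reported at each assessment, orders are extracted for the time before enrolment and over the 24 months, and the baseline variables are already planned. Data collection is expected to run to July 2026. The cost is a little more programming and a more cautious mediation claim.

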**Methods::**

This cluster randomized clinical trial will be conducted to evaluate the impact of an anticholinergic deprescribing intervention compared to usual care on outcomes of cognition and safety in primary care older adults. Participants will include those aged 65 years and over, receiving primary care in the greater Indianapolis area, using a strong anticholinergic within the last two weeks or with evidence of high-risk exposure in the past year. Those excluded will have a diagnosis of Alzheimer’s disease or related dementia, or serious mental illness. The trial plans to enroll 344 participants who will be cluster-randomized at the level of primary care physician to avoid contamination. Participants will complete outcome assessments every six months up to 2 years by blinded outcome assessors. The primary outcome of the study is a composite measure of cognition that includes domains assessing executive cognitive function, language, and memory. Secondary outcomes include patient-reported measures of pain intensity, depression, anxiety, sleep disturbance, and health-related quality of life.

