## Methods

The R2D2 trial primary objective is to determine the efficacy of an anticholinergic deprescribing intervention on cognition compared to usual care in older adults using strong anticholinergics at baseline. The second objective is to examine the quality of life and safety profile of deprescribing compared to usual care. Third, the study intends to determine whether demographic (age, gender, race), genetic (APOE 4 status), or clinical characteristics (comorbidities, number of medications) moderate the effect of the deprescribing intervention.

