The presence of APOE 4 alleles may modify the effect of anticholinergics on cognitive impairment, therefore, we originally planned to collect blood from each participant at baseline to include as a covariate in the responder analysis (secondary aim). However, given the COVID-19 interruption of in-person research, we revised our procedures to collect the APOE 4 variable remotely through saliva samples. Genomic DNA will be extracted from saliva samples using the DNeasy Blood & Tissue Kit (Qiagen, Inc., Valencia, CA) according to the manufacturer’s protocol. Sample kits will be distributed by mail to participant homes with instructions on how to complete and with pre-paid packaging to return to the Indiana Biobank for storage and processing. The sample kit will be distributed at the beginning of the study, but may be completed at any time of participation, and must be completed before 24 months or withdrawal from the study. Extracted DNA will be sent to LGC Limited, the preferred genotyping resource of the Indiana Alzheimer’s Disease Center and the Indiana Clinical and Translational Sciences Institute.

Because individual differences have potential to modify treatment outcomes, we will measure the following demographic and clinical factors: age, self-reported race, self-reported gender, self-reported years of education, and relevant clinical diagnoses impacting cognition such as depression, cardiovascular disease, stroke, and diabetes as we have done in prior studies.^8
17
55^ These demographic variables will be collected at baseline while diagnoses from the electronic medical record will be collected at baseline and 24 months (see Table 1). We will collect medication use through both self-report at baseline and each outcome assessment, and extract prescribed medications (medication orders) from electronic medical records prior to enrollment as well as during the 24-month study period.

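### The moderator analyses are called exploration, but any significant interaction is to be read as a different subgroup effect, across about 36 to 60 tests

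*Protocol article*

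**What the plan says.** The opening of the Methods lists three objectives. The last of them reads: "the study intends to determine whether demographic (age, gender, race), genetic (APOE 4 status), or clinical characteristics (comorbidities, number of medications) moderate the effect".

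The last part of the Analysis Plan describes the method. It opens with "Exploration of potential moderation effects from" APOE or participant characteristics, and proceeds by "including each of these variables and its interaction with the randomization group in the mixed effects models for the outcome measures". It then says how a result will be read: "Significant interactions will indicate significantly different intervention effects in subgroups defined by" those variables. No significance level is attached to these interactions, and no outcome is singled out.

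The outcome measures are the cognitive composite (primary) and five others. The abstract says: "Secondary outcomes include patient-reported measures of pain intensity, depression, anxiety, sleep disturbance, and health-related quality of life". The Measures section adds further candidate modifiers to the six in the objective: "self-reported years of education, and relevant clinical diagnoses impacting cognition such as depression, cardiovascular disease, stroke, and diabetes".

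The article's Type I error statement, also in the Analysis Plan, concerns efficacy and the absence of interim analyses. It does not mention moderation.

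**The concern.** The article gives the moderator work two different standings. As an objective, it is something the trial will determine; in the Analysis Plan, it is exploration. The interpretive sentence sides with the first: a significant interaction is taken to show that the effect differs in that subgroup, with no qualification. Applied across all moderators and all outcomes, that reading is likely to produce at least one subgroup finding by chance alone.

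At stake is what the trial may say about, for example, APOE 4 carriers, one race or one gender, on cognition or on the symptom and quality-of-life scales. A chance interaction could be reported as the answer to a stated objective, and the article's own wording would support that report.

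**Working it through.** **The plan's own figures.** The article gives no error rate for the moderator tests, so there is none to reproduce. Its sample size section concerns group differences, not interactions. From its base of 96 per group, 96 × (1 + 5 × 0.05) = 120, then 120 / 0.70 = 171.4, rounded up to 172, and 2 × 172 = 344, as stated.

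**Inputs**
- Outcomes: the cognitive composite, four PROMIS scores (depression, anxiety, sleep disturbance, pain) and the HUI, so 6.
- Moderators in the third objective: age, gender, race, APOE 4 status, comorbidities, number of medications, so 6.
- Wider count: replacing comorbidities by the four diagnoses named in Measures gives 9; adding education gives 10.
- Level: two-sided 0.05 per interaction. This is an assumption. The article states 0.05 only for the sample size and the Aim 2 calculation.
- Correlations among outcomes and among moderators: not given, so a range is shown.

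**Number of tests.** 6 × 6 = 36; 9 × 6 = 54; 10 × 6 = 60.

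**Expected false positives with no true moderation.** 36 × 0.05 = 1.8; 60 × 0.05 = 3.0. These do not depend on the correlations.

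**Chance of at least one, independent tests.** 1 − 0.95^36 = 84.2%; 1 − 0.95^54 = 93.7%; 1 − 0.95^60 = 95.4%.

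**Chance of at least one, correlated tests.** The table comes from 40,000 simulated sets of null interaction statistics per setting. Each range covers moderator correlations from 0 (upper end) to 0.4 (lower end).

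| Outcome correlation | 6 moderators | 10 moderators |
|---|---|---|
| 0.3 throughout | 75–81% | 88–94% |
| 0.5 throughout | 68–75% | 83–90% |
| PROMIS/HUI 0.5, cognition 0.15 with them | 72–78% | 85–92% |
| 0.7 throughout | 59–66% | 74–83% |
| 0.9 throughout | 43–50% | 57–68% |

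With moderator correlation no higher than 0.2, the last row is 48–50% and 65–68%.

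**Cross-check.** A separate patient-level simulation used 192 effective patients in total, 2,000 trials per setting, cognition correlated 0.2 with the other outcomes and moderators correlated 0.2. For PROMIS/HUI correlations of 0.3, 0.5 and 0.7 it gave 80%, 77% and 69% with six moderators, and 94%, 92% and 87% with ten.

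**Cognitive composite alone.** 1 − 0.95^6 = 26.5% and 1 − 0.95^10 = 40.1% if independent; 22–38% with moderators correlated 0.2 to 0.4.

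Extra terms for the interaction over time, or several contrasts for race, would change the count. They are not included.

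**The case against.** The strongest reply is that the article does call this exploration, and that moderation carries little weight elsewhere. The Background names only a primary and a secondary aim, neither of them moderation, and the abstract, sample size section and Discussion promise nothing about subgroups. On this view the closing sentence merely explains what an interaction term means. The label is real and must be stated, but it does not settle the matter: the sentence draws a conclusion without the limit that the label implies, and the objective uses the language of determination.

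A reader might infer that the lack of a multiplicity correction is itself an error. The documents do not support that. Such detail is commonly left to the statistical analysis plan, which is not shown. The point rests on the interpretive rule that the article does state.

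A reader might also infer that false subgroup claims will occur in some fixed share of trials such as 70 to 95%, or that the third objective cannot be answered. Neither follows. The percentages depend on an assumed level, on how moderators are counted and on assumed correlations, and 70% is not a floor. Nor does the article say it will make one overall claim if any test is significant. It reads each interaction for its own variable, and each such question keeps its own error rate at the assumed 0.05. A reader shown all the tests could recognise about two nominal positives in 36 as chance. That protection depends on all the tests being shown and counted, which the stated rule does not require.

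**Conclusion.** The point holds as a mismatch between an exploratory label and a conclusory rule, made consequential by the number of tests. Assuming an unadjusted 0.05 per interaction, 36 to 60 tests and no true moderation, 1.8 to 3.0 false positives are expected. The chance of at least one is 84–95% under independence, about 70–94% with low to moderate outcome correlation (0.3 to 0.5), and about 48–68% at an outcome correlation of 0.9, falling to 43% in the least favourable setting tried. Even that lowest figure is far above 5%, so the conclusion does not hinge on the exact correlation.

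A reader might take this as a threat to the main result. It is not: the primary efficacy comparison and its Type I error are untouched. What is affected is the reliability of any subgroup statement made under the third objective.

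**What to change.** Replace the closing sentence on moderation in the Analysis Plan with:

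> *Interaction analyses are exploratory and hypothesis-generating; each is reported as an estimate with a 95% confidence interval, the number of interactions examined is stated, and no conclusion of a different effect in a subgroup is drawn from unadjusted significance.*

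Reword the third objective in the Methods to match, for example as exploring whether the listed characteristics moderate the effect.

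If the investigators want to be able to declare a moderator, confine that to the listed moderators on the cognitive composite, with a multiplicity adjustment specified in advance. This is a choice, not a requirement. Its small downside is that a true moderator becomes harder to declare, in a trial not sized for interactions.

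The change needs no new data or participants. The article expects data collection to run to July 2026, so it should be made before the final analysis.
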